## Research aims

The aim is to determine whether a DM-specific OHP (MINDS OHP) will improve the psychosocial health of people with diabetes, compared to usual care. The primary objective is to identify the impact of the OHP on levels of self-efficacy and quality of life for those living with DM. Secondary objectives are to evaluate the impact of the OHP on depression, anxiety, social and workplace functioning, diabetes-related distress, illness perceptions of DM, and coping with DM.

In addition, a health economic cost analysis will be performed, assuming an Australia-wide implementation, to identify any cost savings of the MINDS OHP intervention over current practice. Quality-adjusted life years (QALYs) will be measured using the Assessment of Quality of Life-6D (AQoL-6D) [26] and European Quality of Life-5 dimensions (EQ-5D) [27]. Process evaluation including focus group interviews will also be conducted with participants with diabetes and diabetes clinicians to assess the effectiveness of the MINDS OHP operations, implementation, and service delivery.

## Methods

### General design

This is a prospective randomised controlled trial examining the effectiveness of the OHP specifically adapted for adults with DM, focused on improving participants’ psychosocial health.

The intervention period lasts for 8 weeks with an additional booster session, and is compared with usual care. The study protocol and its amendments were approved by the Human Research Ethics Committee of St Vincent’s Hospital Melbourne (decision number 036/14, 21 April 2015). An executive steering committee (all authors) is responsible for study planning, conduct and monitoring.

### Setting

The study will be conducted at St Vincent’s Hospital, a large metropolitan teaching hospital in Melbourne, Australia. As of March 2015 the endocrinology and diabetes unit had over 1000 people with diabetes enrolled in their patient database: 370 people with type I DM and 1313 with type 2 DM. The necessary volume of clinical cases and expertise required for this study is well established in this unit. As a focus of the OHP is care co-ordination, the program has been integrated into existing services through transparent, planned and close collaboration with the diabetes unit, i.e. diabetes educators, endocrinologists, social workers, and dieticians.

### Participants

A total of 166 participants with a diagnosis of DM will be recruited into the RCT. Inclusion criteria are: (1) have a DM diagnosis, confirmed by medical records; (2) be aged 18 years or above; and (3) be able to converse in English without an interpreter. Exclusion criteria are: (1) presence of developmental disability or amnestic syndrome impairing their ability to learn from the intervention; and (2) comorbid serious acute medical illness defined by the treating physician. As the OHP adopts a holistic approach to managing chronic disease, patients may enter the program at any stage along the continuum of care. De-identified records will be collected on how many people with diabetes were approached or self-referred to the study including reasons for decline, to assess for potential selection bias.

Power was calculated to detect a medium effect size of d = 0.50. This was chosen as a clinically meaningful effect size that may be compared with previous RCT research in the area of chronic disease management programs [28]. The calculations assumed two primary outcomes (health-related quality of life and General Self-efficacy Scale (GSE) scores), four assessment points (baseline, 3-month, 6-month, and 12-month follow-ups), a study-wide type I error rate (α) of .05, and hence a type II error rate (β) of 0.20 (power of 0.80), a correlation of post-treatment scores with baseline measurements (ρ) of 0.81, and a two-tailed statistical test [29]. To detect the effect size of d = 0.50, 66 participants in each of the control and intervention groups will be required. Allowing for up to 20 % attrition, a total of 166 participants, or 83 in each group will be recruited.

### Study procedures

#### Consent

The process of consent will be in accordance with the Declaration of Helsinki. All eligible people with diabetes will be fully informed that they are being asked to participate in an RCT. The procedures involved in the study, and the chances of being assigned randomly to one of two groups will be explained verbally and via an information sheet approved by St Vincent’s Hospital Human Research Ethics Committee. A signed consent form will be obtained from each participant. Participants will be made aware of their right to withdraw from the study at any time without any effects on their usual clinical management.

#### Randomisation and blinding

Using a computer-generated block randomisation sequence created by a person not directly involved in the study, participants will be allocated to treatment or control group. The allocation sequence will be generated using random numbers. Participants will be randomised progressively as they consent. Due to the nature and length of the intervention, it is not possible to mask either participant or investigator to the treatment allocation.

#### Recruitment

Potential participants with DM at St Vincent’s Hospital will be identified by the diabetes clinical staff (e.g. endocrinologist, diabetes educator) and provided with a study flyer. People with diabetes will be asked permission for a researcher to approach them to discuss the program in more detail. If agreeable, people with diabetes will be approached, informed and formally consented by the research assistant. Study flyers will also be posted online through community organisations and will include contact details for the research team. Participants from the community may contact researchers directly to request further information. Recruitment will occur over an 18-month period (see Fig. 2).

**Fig. 2 Fig2:**
[figure not shown]
Flowchart of the Mental Health in Diabetes Services Optimal Health Program (MINDS OHP) randomised controlled trial (RCT)

### Intervention: MINDS OHP

The MINDS OHP is delivered in nine (8 + 1 booster session) sequential sessions based on a structured treatment manual Optimal Health Program: My Workbook (version 3) [30]. The sessions will be one-on-one, delivered face-to-face, and participants in rural and regional areas will have the option of participating in sessions via videoconferencing or telephone. Participants are encouraged throughout the program to identify which areas of DM other health domains upon which they would like to focus. Sessions are approximately 1 hour in duration and held weekly, apart from the ‘booster’ session, which is held 3 months after session 8. Learning is cumulative with each session designed to build on the previous session including tasks to complete between sessions, such as journaling and sleep logs.

In summary, session 1 introduces the OHP within the six domains of the Optimal Health Wheel: social, physical, emotional, intellectual, employment (engagement) and spiritual/values. This session provides participants with the opportunity to explore and understand their DM and other health priorities from a holistic perspective. Sessions 2 and 3 initiate development of a health plan exploring the implications and potential complications of DM in terms of strengths and vulnerabilities. In session 3, further understanding is developed around the effects of stress or blood glucose levels with strategies to mitigate these stressors and informing their health plans. Session 4 focuses on metabolic monitoring and medication management (e.g. use of insulin pumps). Session 5 expands the health plan to include key DM partnerships and supports in the community and online, for example Diabetes Australia [31], and HypoActive [32]. Change enhancement is the focus in session 6, in terms of understanding past events and establishing new proactive avenues for change. The aim of session 7 is goal setting via creative problem solving and planning around the complexities of DM. Session 8 strategises DM health and emergency care planning that incorporates wellbeing maintenance and sustainability. The goal of the ‘booster session’ (session 9) is to review health plans, consolidate progress, and reflect on achievements towards health-related goals.

A facilitator with a health background (e.g., nurse, psychologist) will conduct each session. All facilitators will complete a 2-day workshop plus regular supervision and fidelity checks. Facilitators will draw on DM-specific information in concordance with individual circumstances. Examples include the relationship between stress and hypoglycaemia, availability of DM supports in the community, and coping strategies for addressing anxiety related to changes in BSLs. The emphasis is on collaboration between facilitator and participant to arrive at program goals that stem from the participant’s main concerns and needs. The facilitator will encourage participants to identify their early warning signs of stress and illness and integrate healthy coping strategies to prevent stress build-up. Facilitators may also discuss and arrange referrals for other services in conjunction with the multidisciplinary team depending on participant needs. Additionally, facilitators may work with the multidisciplinary team to coordinate visits with other hospital appointments.

### Control

The comparison group will receive usual care and no MINDS OHP intervention. As participants will be recruited from a variety of settings (hospital outpatients, community organisations) we anticipate variation in standard care received. To capture this variation, all participants will complete the Health Care Utilisation Questionnaire (HCUQ) [33] at each time point. Participants in the control group will have the option of completing the MINDS OHP at the end of the trial once evaluation is complete.

### Outcome measurements

Table 1 displays primary and secondary outcome measures and time points. Primary measures are changes in: health-related quality of life as assessed by the AQoL-6D [26], consisting of six separately scored dimensions of good health and a simple global ‘utility’ score and EQ-5D [27]; and self-efficacy as measured by the General Self-Efficacy Scale (GSE) [34], a general sense of perceived self-efficacy in regarding daily hassles as well as adaptation to stressful life events. Secondary measures are: the Diabetes Quality of Life (DQoL) [35] measure, a screen for problem or risky substance use in adults as assessed by the Alcohol, Smoking and Substance Involvement Screening Test (ASSIST) [36] developed by the World Health Organization (WHO); coping strategies as measured by an abbreviated version of the COPE inventory [37], the Brief COPE [38]; treatment expectancy and rationale credibility in clinical studies as assessed by the Credibility/Expectancy Questionnaire (CEQ) [39]; clinical indices such as body mass index (BMI) and glycated haemoglobin (HbA1c); diabetes-related psychosocial self-efficacy measured by the Diabetes Empowerment Scale (DES) [40]; symptom severity and caseness (number meeting clinical disorder threshold) of anxiety and depression as assessed by the Hospital Anxiety and Depression Scale (HADS) [41]; health care utilisation for economic evaluation purposes assessed by the Health Care Utilisation Questionnaire (HCUQ) [32]; diabetes-related emotional distress measured by the Problem Areas in Diabetes Scale (PAID) [42]; perceived acceptability of treatment assessed using the Treatment Evaluation Inventory-Short Form (TEI-SF) [43]; a 10-item measure of the Big Five Inventory (BFI) personality dimensions [44]; and impact of a person’s mental health difficulties on their ability to function via the Work and Social Adjustment Scale (WSAS) [45].

**Table 1 Tab1:** Primary and secondary outcome assessments and time points for MINDS

Assessment tools	Baseline	3-month	6-month	12-month
Primary outcomes				
AQoL-6D (20 items)	X	X	X	X
GSE (10 items)	X	X	X	X
Secondary outcomes				
DQoL (15 items)	X	X	X	X
ASSIST (6 items)	X	X	X	X
Brief COPE (28 items)	X	X	X	X
CEQ (6 items)	X			
Clinical Indices (e.g. BMI)	X	X	X	X
DES (8 items)	X	X	X	X
EQ-5D-3L (6 items)	X	X	X	X
HADS (14 items)	X	X	X	X
HCUQ (17 items)	X	X	X	X
PAID (20 items)	X	X	X	X
TEI-SF (9 Items)		X		
BFI-10 (10 items)	X			
WSAS (5 items)	X	X	X	X

*AQoL-6D* Assessment of Quality of Life-6 Dimensions [26], *GSE* General Self-efficacy Scale [34], *DQoL* Diabetes Quality of Life [35], *ASSIT* Alcohol, Smoking and Substance Involvement Screening Test [36], *Brief COPE* abbreviated version of the COPE Inventory [38], *CEQ* Credibility/Expectancy Questionnaire [39], *BMI* body mass index, *DES* Diabetes Empowerment Scale [40], *EQ-5D-3L* European Quality of Life-5 Dimensions-3 Levels [27], *HADS* Hospital Anxiety and Depression Scale [41], *HCUQ* Health Care Utilisation Questionnaire [33], *PAID* Problem Areas in Diabetes Scale [42], *TEI-SF* Treatment Evaluation Inventory-Short Form [43], *BFI-10* Big Five Inventory-10 item [44], *WSAS* Work and Social Adjustment Scale [45]

Due to variability of usual care across all participants, key aspects of usual care will be assessed via responses on the HCUQ [32]. If possible, medical records will be reviewed to ascertain DM diagnostic information and clinical indicators such as HbA1c.

### Program assessment and treatment fidelity

The OHP facilitators will receive training, a structured manual/protocol, and monthly group supervision with the clinical investigators (with individual supervision provided as needed in between group sessions). The purpose of supervision will be to discuss problems in study procedures and ensure standardised activity. The OHP sessions will be audio recorded with a random selection rated by independent assessors according to compliance with OHP protocols. Identified variations from protocols will be communicated back to the facilitator. In addition, content of sessions including participant needs and concerns will be raised at supervision meetings. All facilitators will complete a summary of each session using a standard template and send these notes to the research team. Session notes will include OHP topics covered, participant concerns raised, and needs for supervision.

Post-intervention focus groups will be held for clinicians and for participants from the control and intervention groups. Participants will be informed that the purpose of the focus group is to gain an in-depth understanding of their experiences of the study, advantages and disadvantages of conducting the study/program in their services (for service providers), and suggestions for components to include or exclude from the OHP. To increase objectivity, focus group facilitators will be independent researchers who were not OHP facilitators.

### Statistical analyses

Intention-to-treat analyses will be employed to prevent overestimation of efficacy. Categorical variables will be analysed using chi-squared tests (or Fisher’s exact test for small samples). A mixed-effects model, repeated measures (MMRM) approach will be used to examine the longitudinal profile of all continuous variables at 3, 6 and 12 months post-baseline. For all MMRM analyses, baseline scores will be used as covariates and the models will include prespecified fixed effects of treatment, clinician, and time, and treatment-by-time and treatment-by-clinician interactions.

Secondary analyses using analysis of covariance will be conducted to compare change scores during treatment and follow-up phases for all primary, secondary, and process outcomes using the fixed, continuous covariate of baseline score and time from diagnosis as well as the categorical fixed effects of treatment group, clinician, and treatment-by-clinician interactions. Sub-analyses will be conducted on participants with T1 and T2DM as these have different disease processes and aetiologies.

Although the attrition rate is not expected to vary by treatment condition, we will attempt to identify key predictors of attrition status (i.e. demographic and baseline clinical characteristics) and test for differences between conditions. Assuming the data are missing at random, several procedures offer effective approaches that may attenuate attrition. Maximum likelihood models (i.e. MMRM), with time as a random variable, allow the use of all available data from all assessments, reducing bias and increasing power [46]. In addition, multiple imputation procedures that utilise the expectation-maximization (EM) algorithm with bootstrap estimates of standard errors will be used to address attrition. The application of these procedures can provide unbiased estimates, even in the face of substantial missing data [47].

A full economic evaluation will occur alongside the proposed RCT. Healthcare outcomes and costs will be compared between participants in control and interventional conditions. Healthcare system (medical record) and self-reported information via the HCUQ [32] will be used to generate analyses. The utility measurements of participant quality of life will be assessed using AQoL-6D [26] developed in Australia and the EQ-5D-3L [40] developed in Europe. The potential long-term (lifetime) impact on cost and effectiveness of intervention beyond the trial period will be extrapolated using the Markov process modelling method.

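### HADS caseness, a repeated binary secondary outcome, is assigned an unadjusted chi-squared or Fisher test, which gives up power that its own baseline measurement could recover

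*Protocol article*

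**What the plan says.** All of this is in the protocol article.

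- **Outcome measurements** lists among the secondary measures the "symptom severity and caseness (number meeting clinical disorder threshold) of anxiety and depression", taken from the HADS. One questionnaire thus yields a continuous score and a yes/no outcome. Table 1 schedules it at baseline, 3, 6 and 12 months.
- **Statistical analyses** says "Categorical variables will be analysed using chi-squared tests", or Fisher's exact test where samples are small. No covariate and no visit term is attached.
- The same section says that the MMRM "will be used to examine the longitudinal profile of all continuous variables at 3, 6 and 12 months post-baseline", and that "For all MMRM analyses, baseline scores will be used as covariates".
- It adds a secondary analysis of covariance to "compare change scores during treatment and follow-up phases for all primary, secondary, and process outcomes".
- On missing data, it plans multiple imputation "with bootstrap estimates of standard errors will be used to address attrition". This is not limited to continuous outcomes.
- The general principle is that "Intention-to-treat analyses will be employed to prevent overestimation of efficacy".

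**The concern.** The two halves of the HADS outcome are treated unequally. The severity score gets a model that uses the baseline score and all visits. The caseness indicator, derived from the same items on the same dates, gets a two-by-two comparison that uses neither.

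The entry criteria in the Participants section set no distress threshold, so cases and non-cases may both be enrolled. Baseline status should then predict follow-up caseness, and a test that ignores it leaves explainable variation in the error.

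What is at stake is the chance of detecting a real effect on anxiety or depression caseness. The method is stated in the article, so an analysis plan that follows the article would inherit it. The secondary analysis of covariance does not repair this: it models change scores, and change in a yes/no variable can only be -1, 0 or 1.

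**Working it through.** **1. The plan's own figure.** Inputs from the Participants section: d = 0.50, study-wide two-sided alpha 0.05 over two primary outcomes (0.025 each if split equally), power 0.80, four assessments, correlation 0.81, attrition 20%.

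- Two-sample size at alpha 0.025: 77 per arm.
- Repeated-measures factor: (1 + 3 × 0.81)/4 = 0.8575.
- 77 × 0.8575 = 66.0 per arm, as stated.
- 66/0.80 = 82.5, rounded up to 83 per arm, as stated.

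The sample size reproduces. From it the check below takes 66 analysed per arm, a shift of 0.50 SD and a correlation of 0.81. The protocol states these for the primary outcomes, so applying them to the HADS is an assumption.

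**2. Caseness rates.** The document gives none. Control caseness p is assumed to be 20%, 30% or 40%. If caseness means exceeding a threshold on a latent normal score, a downward shift of 0.50 SD gives treated caseness 1 − Φ(Φ⁻¹(1 − p) + 0.50):

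- p = 0.20: 1 − Φ(0.842 + 0.50) = 0.090
- p = 0.30: 1 − Φ(0.524 + 0.50) = 0.153
- p = 0.40: 1 − Φ(0.253 + 0.50) = 0.226

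**3. Chi-squared power by formula** (one visit, two-sided 0.05, n = 66 per arm):

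Power = Φ{[|p₁ − p₂|√n − 1.96√(2p̄(1 − p̄))] / √(p₁(1 − p₁) + p₂(1 − p₂))}

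For 0.30 against 0.153, p̄ = 0.2265: (0.147 × 8.124 − 1.96 × 0.592)/0.583 = 0.058, so power is 0.52. The other two rates give 0.43 (p = 0.20) and 0.58 (p = 0.40).

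**4. Effect of baseline adjustment, by simulation.** There were 1,500 simulated trials per setting. Baseline b is standard normal; follow-up is ρb + √(1 − ρ²)e, minus 0.50 in the treated arm; both are cut at the same threshold. The chi-squared test is compared with the likelihood-ratio test from logistic regression.

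| ρ | Control caseness | Chi-squared | Adjusted for baseline caseness | Adjusted for baseline score |
|---|---|---|---|---|
| 0.81 | 20% | 0.44 | 0.58 | 0.66 |
| 0.81 | 30% | 0.53 | 0.69 | 0.75 |
| 0.81 | 40% | 0.58 | 0.76 | 0.83 |
| 0.50 | 20% | 0.43 | 0.46 | 0.49 |
| 0.50 | 30% | 0.53 | 0.57 | 0.60 |
| 0.50 | 40% | 0.58 | 0.64 | 0.65 |

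Taken from the unrounded results, the gain at ρ = 0.81 is 14 to 18 points with baseline caseness and 22 to 26 with baseline score. At ρ = 0.50 it is 3 to 6 points and 6 to 7 points.

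A second setting (83 per arm, 20% loss, 30% caseness, shift 0.4 SD, baseline score as covariate) gave 0.36 against 0.41 at ρ = 0.5, 0.40 against 0.46 at 0.6, and 0.39 against 0.60 at 0.81. The gains are 5, 6 and 21 points.

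**5. Validity.** With no effect and full data, chi-squared rejected in 4.6 to 5.5% of trials and the adjusted tests in 4.9 to 6.1%. The simulation error here is about √(0.05 × 0.95/1500) = 0.6 points. The adjusted test may be very slightly liberal, but not by enough to explain the gain at ρ = 0.81.

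**The case against.** **The consequence is limited.** Caseness is one part of one secondary measure. Severity comes from the same questionnaire and already has the baseline-adjusted MMRM, so the anxiety and depression objective does not depend on caseness. This stands, and it limits the weight of the point.

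**The large gain needs a high correlation.** The 0.81 is stated for the primary outcomes, not for the HADS. This stands too; at 0.5 to 0.6 the gain is modest.

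**The sentence is generic and a SAP may say more.** It does not name caseness. But it is the only method given for categorical variables, and the next sentence confines the MMRM to continuous ones. That is a stated choice rather than detail left out. Visit-by-visit comparisons are not wrong in themselves; the weakness is the missing baseline term.

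**Two stronger readings are not supported.** A reader might infer that the chi-squared test conflicts with the intention-to-treat statement. It does not: comparing arms as randomised is compatible with intention-to-treat whether or not a covariate is used, and missing data are a separate matter.

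A reader might also infer that drop-out is ignored and that caseness results will be biased. The article plans multiple imputation without excluding categorical outcomes, and nowhere says that the chi-squared test is restricted to completers. Even a completers-only test kept its error rate in simulation when drop-out was equal (5.6%) or depended on baseline caseness alike in both arms (5.0%). Bias would need a completers-only test together with severity-related drop-out that differs by arm. The article does not expect attrition to differ by arm and plans to test whether it does.

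**Conclusion.** The point holds as one of efficiency. The stated method for HADS caseness is valid but leaves out a baseline measurement that the trial already collects. The loss is about 14 to 26 points of power if the baseline correlation is as high as 0.81, and about 3 to 7 points at 0.5 to 0.6, depending on the baseline term and setting.

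These sizes rest on assumed caseness of 20 to 40%, a latent normal score, a borrowed effect size and correlation, and a single visit. The full repeated-measures model was not simulated. Adjustment raised power in every setting tried; only the amount is uncertain. The primary outcomes and the HADS severity analysis are unaffected, and neither a breach of intention-to-treat nor a neglect of drop-out is shown.

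**What to change.** In the Statistical analyses section, separate repeated binary outcomes from other categorical variables:

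- Analyse repeated binary outcomes such as HADS caseness with a logistic mixed model or GEE containing treatment, visit, treatment-by-visit and the baseline HADS score. The score recovered more power than baseline caseness in every setting above.
- State that the multiple imputation already planned applies to these outcomes. This matters particularly for GEE, which without imputation or weighting generally relies on a stricter missing-data assumption than the MMRM.
- Report visit-specific odds ratios together with standardised risk differences. Say whether the odds ratio is conditional (mixed model) or marginal (GEE), since the two differ in size.
- Keep chi-squared or Fisher's exact test for one-off descriptive comparisons.

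The cost is slightly more analysis work and a short change of text. No extra participants, visits or data are needed.

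### The MMRM omits time from diagnosis, which the secondary ANCOVA of the same outcomes adjusts for, and no reason is given: a minor inconsistency worth aligning

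*Protocol article*

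**What the plan says.** All of this is in the protocol article; no separate analysis plan is shown.

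- **MMRM (Statistical analyses).** For every continuous outcome at 3, 6 and 12 months: "baseline scores will be used as covariates and the models will include prespecified fixed effects of treatment, clinician, and time". Interactions of treatment with time and of treatment with clinician complete the model.
- **ANCOVA (Statistical analyses).** Introduced as secondary, for change scores on all primary, secondary and process outcomes, "using the fixed, continuous covariate of baseline score and time from diagnosis". Treatment group, clinician and their interaction enter as categorical terms.
- **Randomisation and blinding.** "Using a computer-generated block randomisation sequence created by a person not directly involved in the study". No stratification factor is named.
- **Control.** The article expects usual care to differ because participants are "recruited from a variety of settings (hospital outpatients, community organisations) we anticipate variation in standard care received". The HCUQ, given to everyone at each assessment, is the planned record of that variation.

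Treatment, clinician and their interaction are in both models. Time and treatment-by-time belong to the repeated-measures structure of the MMRM. Among participant-level baseline covariates, the only difference is time from diagnosis: in the ANCOVA, not in the MMRM.

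**The concern.** The article is not silent on covariates. It states both lists and calls the MMRM effects prespecified, so this is a choice made in the text rather than a detail left for later. The fuller adjustment sits in the supporting analysis and the leaner one in the main analysis, without a reason.

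Two things are at stake, both modest. First, if time from diagnosis predicts self-efficacy or quality of life beyond the baseline score, the main estimate is slightly less precise than it could be. A chance imbalance in disease duration would also stay in the main estimate while being adjusted out of the secondary one. A wide spread in duration is plausible, because the Participants section admits people at any stage of care.

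Second, the two analyses are harder to compare. If MMRM and ANCOVA disagree on an outcome, a reader cannot tell whether the method or the covariate set is responsible.

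**Working it through.** **Step 1. Does the point touch the sample size?** Inputs from the Participants section: d = 0.50, two primary outcomes, study-wide α = 0.05, power 0.80, two-tailed, ρ = 0.81, four assessment points, 66 per arm, 20% attrition, 166 in total. The article prints no formula. One that reproduces the figure assumes an equal α split (0.025 each) and the mean of m = 4 equally correlated measures:

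n per arm = 2 × ((z₀.₉₈₇₅ + z₀.₈₀)/d)² × (1 + (m − 1)ρ)/m

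- 2 × ((2.2414 + 0.8416)/0.50)² = 76.04
- (1 + 3 × 0.81)/4 = 0.8575
- 76.04 × 0.8575 = 65.2, rounded up to 66
- 66/(1 − 0.20) = 82.5, rounded up to 83; 2 × 83 = 166

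The stated figures reproduce, and time from diagnosis plays no part in them.

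**Step 2. How much variance is left to explain?** At ρ = 0.81 the baseline score removes 0.81² = 65.6% of single-visit variance and leaves 34.4%. Any further covariate can act only on that remainder.

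**Step 3. Effect of adding one covariate.** The article gives no prognostic strength for time from diagnosis, so the partial R² beyond the baseline score is assumed over 0 to 0.10. Residual variance is multiplied by (1 − R²). Estimating one more coefficient with 132 evaluable participants costs a factor of about 127/126 = 1.0079 (degrees of freedom and chance collinearity). The power column starts from exactly 80% at α = 0.025.

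| Assumed partial R² | Variance ratio (1 − R²) × 127/126 | Change in SE | Power |
|---|---|---|---|
| 0 | 1.008 | +0.4% | 79.7% |
| 0.01 | 0.998 | −0.1% | 80.1% |
| 0.02 | 0.988 | −0.6% | 80.5% |
| 0.05 | 0.958 | −2.1% | 81.8% |
| 0.10 | 0.907 | −4.8% | 84.0% |

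Break-even is at R² = 1 − 126/127 = 0.8%.

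**Step 4. Effect of a chance imbalance.** With 66 evaluable per arm, the SD of a standardised imbalance is √(2/66) = 0.174, so a 1.96-SD imbalance is 0.34 SD of the covariate. The shift in the unadjusted estimate is √(R² × 0.344) × 0.34:

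- R² = 0.01: 0.059 × 0.34 = 0.02 SD
- R² = 0.05: 0.131 × 0.34 = 0.04 SD
- R² = 0.10: 0.185 × 0.34 = 0.06 SD

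For comparison, the single-visit SE is √(0.344 × 2/66) = 0.10 SD. Even an unusually large imbalance moves the estimate by less than one standard error.

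**The case against.** The strongest case against is that nothing here is an error. A main model adjusted for the baseline score, followed by a secondary ANCOVA with one more covariate, is an ordinary design. Both are prespecified and both give a valid randomised comparison. The Outcome measurements section says records will be reviewed for diagnostic information only where possible, so keeping this variable out of the main model could be deliberate. A single linear slope for duration across type 1 and type 2 diabetes is also a simplification.

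Much of this stands. It makes the point minor, but it does not supply the missing reason. Gaps in diagnosis dates affect the planned ANCOVA just as much, and so does the single slope.

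A reader might infer more than the documents support:

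- **That the MMRM adjusts for nothing except the baseline score.** It also contains clinician and treatment-by-clinician terms. The statement is true only of participant-level baseline covariates.
- **That the added precision is free.** It is not: below a partial R² of about 0.8% the SE rises slightly.
- **That chance imbalance biases the main result.** Under randomisation it neither biases the comparison on average nor inflates the type I error, and the SE already reflects it. Adjustment improves conditional precision only.
- **That recruitment setting must also be in the models.** The Control section expects standard care to vary across settings. It does not say that setting predicts GSE or AQoL-6D scores given baseline. Adjusting for setting is optional, and leaving it out is not an error. Post-baseline HCUQ responses would not be suitable adjusters.

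**Conclusion.** The point holds as a minor inconsistency. The main and secondary analyses of the same outcomes use different participant-level covariates, without a stated reason, and the sponsor's own chosen adjuster is missing from the main one. Neither the validity of the test nor the 166 participants is affected.

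The likely gain runs from about nil at a partial R² near 1% to an SE reduction of about 2% at 5%, or roughly 2 points of power from 80%. These figures rest on an assumed prognostic strength, on ρ = 0.81 carrying over to the trial data, and on 132 evaluable participants. The firmer benefit needs no such assumption: with a common participant-level set, a difference between MMRM and ANCOVA can no longer come from the choice of baseline covariates.

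**What to change.** In the MMRM sentence under Statistical analyses, name baseline score and time from diagnosis as the covariates, matching the ANCOVA. State how a missing diagnosis date is handled in both models, for example by a self-reported year of diagnosis collected at baseline or by simple covariate imputation that ignores treatment arm, so that no randomised participant is dropped. If the sponsor prefers to keep the sets different, one sentence giving the reason would be enough. Either change should be made before any outcome data are examined by arm.

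Cost: one sentence, one model degree of freedom, an SE increase of about 0.4% if the covariate proves unrelated to outcome, and some work on missing diagnosis dates that the planned ANCOVA needs anyway.
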